### Quality control

Half a month before the implementation of the research, researchers of Peking University will conduct training to CBO staffs in following aspects: (1) the usage of the “Golden ark” app’s function modules, (2) participants recruitment process, (3) HIV and STDs testing methods, (4) answers of frequently asked questions, (5) work quality requirements. After completing the training and passing the test, staff of CBO will be given a staff IDs and conduct the participants recruitment work.

During the implementation of the research, quality control will include three parts: quality control conducted by CBO, quality control conducted by researchers, and quality control conducted by expert committee.

Quality control conducted by CBO includes: (1) The leader of the CBO should check whether the participants’ information records are complete and correct every 2 weeks. The focus is on whether the recruited participants meet the inclusion criteria and have completed the informed consent and the baseline questionnaire. (2) The leader of the CBO should check at least 10 cases of HIV and STDs testing services every month, to see whether the testing operation and input of test results are correct. The above quality control implementation should be recorded and submitted to researcher of Peking University for inspection. (3) Record any harms reported by participants, including psychological and emotional problems and any privacy information disclosure risk, and then report these harms to the research team timely.

For quality control conducted by researchers, it includes the following three aspects: (1) Perform regular backups of data in the database, including HIV and STDs testing records, questionnaire records and queries records. (2) Provide weekly feedbacks to CBO on the list of participants with incomplete information through information system, and respond to the reported harms. (3) Go to the study sites of CBO every 3 months, and conduct spot checks on at least 5% of the staff’s operation, including participants recruitment, HIV and STDs testing services. Interviews with three to five participants will be conducted each time to know more about the issues in the research process.

The expert committee will conduct meetings every 6 months, who will review the annual data analysis reports, the interim analysis reports and reports of potential harms to identify the problems in the research and propose corrective actions. If the effectiveness of the intervention is already significant before the endpoint of this 2.5-years trial, or unexpected harms have been caused to participants, the committee will discuss and make the decision of whether to terminate the trial.

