## Methods/design

### Study design and timeline

This research will use a stepped wedge cluster randomized controlled trial (SW-CRCT) design. It is commonly used to evaluate service delivery or policy interventions of clusters [26]. This research will be implemented in Beijing, whose sixteen districts are defined as the clusters. We assign the sixteen districts into four research groups using stratified randomization, with four districts in one group. The open cohort SW-CRCT will last 2.5 years, which is anticipated to be conducted from July, 2020 to December, 2022. Five continuous observational periods at a 6-month interval are divided. According to the standard design of SW-CRCT, in the first 6-month “the initial period”, no group is exposed to the additional partner notification intervention. After that, the four groups begin to cross from the control condition to receive the partner notification intervention sequentially at 6-month intervals. Once one group receives the partner notification intervention, the intervention will continue until the end of the research. And at the last 6-month period, all of the four groups will receive the additional partner notification intervention. (Fig. 1).

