### Sample size

We used the *steppedwedge* procedure in Stata software set for SW-CRCT design to calculate the sample size. We assumed the HIV incidence was 7% in the control status, and could be reduced to 5% after partner notification intervention. The parameters set for sample size calculation include: (1) The number of clusters was 16; (2) The number of steps was 4, with 4 clusters in one step; (3) α was set as 0.05; (4) Power was set as 0.90; (5) ICC (ρ) was set as 0.01. The total sample was 4320 (270 for each clusters). Considering most studies of MSM showed a high proportion of loss to follow up, we set a 30% loss to follow up in this research. The total sample size was 6172.

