If one variable is missing for < 10% of participants, we will use a complete-case approach. If one variable is missing for 10 ~ 20% of participants, multiple imputation will be used if suitable; if one variable is missing for > 20% of participants, we will investigate the mechanism of missing data, and consider to set the missing data as a category.

A two-sided *p* value of 0.05 or less was regarded as significant. Statistical analyses will be done with SPSS version 21.0, Stata version 24.0, R version 3.5.1. Social network visualization will be done with Cytoscape version 3.5.1.

The results of this research will be reported to local and national stakeholders in the form of oral presentation on professional conferences and publications on journals. We will not use professional writers in writing related articles and reports. The decisions of authorship will follow conventions of the International Committee of Medical Journal Editors. We will share our study protocol, statistical analysis plan, informed consent form, study report and analytic code after completing the analysis of the whole study. If other researchers want to apply for the above information and data of this research, they should contact principal investigator. Personal information (name, unit, title, etc.), detailed description of required data (required variables, etc.), and research proposal are needed for further discussion and decision.

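### Early termination can be considered once the effect is significant, with 0.05 the only stated level: type I error reaches about 12% with four such looks

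*Protocol article*

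**What the plan says.** Three places in the protocol article bear on this.

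- **Quality control.** "The expert committee will conduct meetings every 6 months", and its members are the ones "who will review the annual data analysis reports, the interim analysis reports and reports of potential harms". The trigger follows: "If the effectiveness of the intervention is already significant before the endpoint of this 2.5-years trial", or if unexpected harm has occurred, "the committee will discuss and make the decision of whether to terminate the trial".
- **Analysis.** The only significance threshold in the article is this: "A two-sided *p* value of 0.05 or less was regarded as significant".
- **Sample size.** "α was set as 0.05", with power 0.90 and no allowance for interim testing.

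Study design and timeline sets five 6-month periods over 2.5 years. The first is control only, and four groups of four districts then cross over in turn. The same section defends the design partly on the ground that every cluster and participant will get the intervention.

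**The concern.** The article states an efficacy trigger for termination, and the only level it attaches to significance is the one used at the final analysis. Several tests at 0.05 on accumulating data do not have an overall error of 0.05. No part of the 0.05 is held back for interim looks.

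The claim at stake is the primary one, that partner notification lowers HIV incidence. A stepped wedge is a poor setting for an uncorrected early look: at month 12 only one group of four (4 of 16 districts) has crossed over, with 6 months of exposure. An estimate that is reported because it crossed a threshold on little information tends to be too large.

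**Working it through.** **Inputs from the article.** 16 clusters, 4 steps, 5 periods, 7% against 5%, ICC 0.01, alpha 0.05, power 0.90, 270 per cluster, 30% loss to follow-up.

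**Step 1: the plan's own figure.** The Hussey-Hughes variance of the effect is

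Var = I·s²(s² + T·τ²) / [(I·U − W)s² + (U² + I·T·U − T·W − I·V)τ²],

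where I is clusters, T periods, U the number of treated cluster-periods, W the sum over periods of squared treated-cluster counts, and V the sum over clusters of squared treated-period counts. Take 270 per cluster in each period and total variance 0.07 × 0.93 = 0.0651. Then s² = 0.99 × 0.0651/270 = 0.0002387, τ² = 0.000651, Var = 0.00003805 and SE = 0.00617. Power = Φ(0.02/0.00617 − 1.96) = Φ(1.28) = 0.900. Also 16 × 270 = 4320, and 4320/0.7 gives 6172. Both figures reproduce at an undivided 0.05, with 270 read as the number per cluster-period.

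**Step 2: information at each possible look.** Month 6 has no intervention data, so the earliest possible test is at month 12. I applied the same formula to the design truncated at each look, with variance 0.06 × 0.94 = 0.0564 and τ² = (0.01/0.99) × 0.0564 = 0.0005697. The variance level cancels from the fractions. At 270 per cluster-period s² = 0.0564/270 = 0.0002089.

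| Look (month) | T | U, W, V | Var | Fraction |
|---|---|---|---|---|
| 12 | 2 | 4, 16, 4 | 0.0001206 | 0.28 |
| 18 | 3 | 12, 80, 20 | 0.0000560 | 0.60 |
| 24 | 4 | 24, 224, 56 | 0.0000385 | 0.86 |
| 30 | 5 | 40, 480, 120 | 0.0000333 | 1 |

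If 270 is instead spread over five periods (54 each), the fractions are 0.31, 0.67, 0.93 and 1.

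**Step 3: overall error.** Null z-paths with these fractions were simulated (4 million). A path counts if |z| exceeds 1.96 at any look. The schedules are assumptions.

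| Tests at two-sided 0.05 | Overall type I error |
|---|---|
| Month 30 only | 5.0% |
| One interim look plus month 30 | 6.2% to 9.0%, by timing |
| Months 12, 24, 30 | 9.9% to 10.4% |
| Months 12, 18, 24, 30 (54 per cluster-period) | 11.5% |
| Months 12, 18, 24, 30 (270 per cluster-period) | 12.1% |
| Four equally spaced looks | 12.6% |

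These are two-sided rates. For four looks, roughly half (about 6%) would be false claims of benefit, against 2.5% nominally.

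**Step 4: size of an early significant estimate.** At month 12, with 270 per cluster-period, SE = √0.0001206 = 0.0110. Significance then needs an estimate beyond 1.96 × 0.0110 = 0.0215, or 2.15 percentage points. The planned effect is 2 points, so any significant estimate of benefit at that look would exceed it.

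**The case against.** The best defence is that the article does not say each interim look is tested at 0.05. The trigger is under Quality control and the threshold under Analysis, and joining them is an inference. A boundary could sit in an analysis plan or committee charter that is not shown, and an article need not carry such detail.

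Part of this stands. The number and timing of efficacy analyses are not given: six-monthly is how often the committee meets, and the reports include annual ones. Termination is discretionary, so the four-look figure is the chance that at least one look reaches p of 0.05 or less, which is an upper value for that schedule.

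The rest does not stand. The trigger is stated without qualification, the article gives one meaning of significant, and the sample size uses all of the 0.05. A boundary held elsewhere would have to override the published wording. Discretion does not control error when no criterion limits it.

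A reader might draw three stronger conclusions that the document does not support:

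- *The plan has a 12% error rate.* That needs all four looks, each at 0.05, with stopping at the first crossing. The article fixes none of these.
- *Five looks, hence 14.2%.* No group is exposed in the first period, so there is nothing to test at month 6.
- *Later groups would never receive the intervention after an early stop.* The article does not say what happens to districts not yet crossed over; ending the evaluation need not mean withholding the app function.

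**Conclusion.** The concern holds: this is a stated rule that is badly fixed. Overall type I error would be up to about 12% (11.5% to 12.6%) if efficacy were tested at 0.05 at months 12, 18, 24 and 30 with stopping at the first crossing. It would be about 6% to 10% with fewer looks. Every schedule with an interim efficacy test at 0.05 exceeds 5%.

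The range rests on assumed look times and equal numbers in every cluster-period. Recruitment that builds up gradually in this open cohort would lower the early information fractions and could move the rate modestly upward. The direction of the finding does not depend on these details. The tendency to overestimate is greatest at month 12, when about 28% to 31% of the final information is in.

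**What to change.** Choose one of two changes before any interim look; the article reports that recruitment had not begun.

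1. **Remove the effectiveness trigger**, so that no efficacy claim is made at an interim look. The review of harms is unaffected. This is a one-sentence edit and costs no alpha or power.
2. **Keep efficacy looks but control them.** State their number and timing, use an O'Brien-Fleming-type alpha-spending boundary at the stepped-wedge information fractions, and test the final analysis at the remaining alpha. For four equally spaced looks, nominal two-sided levels of this shape are about 0.00005, 0.0042, 0.019 and 0.043. At the 54-per-cluster-period fractions they are about 0.0002, 0.012, 0.033 and 0.040. Spending should follow the information actually accrued.

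The cost of the second option is a slightly lower final alpha and power, so power should be restated. From Step 1, 0.02/0.00617 = 3.24. At a final level of 0.040 (critical value 2.05), power at the last look alone is Φ(3.24 − 2.05) = Φ(1.19) = 0.88 instead of 0.90, and a little higher once early crossings are counted.

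Under either option, reconcile the termination wording in Quality control with the statement in Study design and timeline that all clusters and participants receive the intervention.

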### Outcomes

The primary outcomes of this research are the HIV positive seroconversion rate (HIV incidence) and the additional cost of the intervention. The HIV positive seroconversion rate is calculated as the number of HIV positive seroconversions divided by the total number of person-years. The additional cost of the intervention is calculated as the total cost and average cost for per participant of the integrated intervention model and each additional intervention/service based on the existing HIV prevention measures provided as before.

The second outcomes of this research include: (1) Positive seroconversion rate (incidence) of syphilis, hepatitis B, and hepatitis C. These indicators are calculated separately as the number of syphilis/hepatitis B/hepatitis C seroconversions divided by the total number of person-years. (2) HIV and related STDs transmission among social networks. Based on the partner notification information, we will construct the transmission networks of HIV and other STDs (syphilis, hepatitis B, and hepatitis C) among participants, and analyze the characteristics of these networks and factors associated with transmission of these diseases. (3) Testing adherence. This indicator is calculated as the proportion of participants whose every adjacent testing interval is no more than 3 months as recommended by China CDC. (4) Additional cost for finding per seroconversion. This indicator is calculated through the total additional cost of the integrated intervention model based on the existing HIV prevention measures provided as before divided by the total number of the HIV and STDs seroconversions. (5) Frequency of utilization for each intervention/service. This indicator is calculated through the total and average frequency of utilization for each intervention/service, such as health education, partner notification, HIV and STDs testing and so on. (6) Satisfaction of the interventions and services, measured through the follow-up questionnaires by the degree of satisfaction for participants of HIV and STDs testing service, health education, partner notification and other app’s functions. (7) Knowledge of HIV and related STDs. This indicator is measured by the baseline and follow-up questionnaires. The score of knowledge questions in the questionnaires will be used to represent participants’ level of knowledge. (8) Health self-responsibility awareness, including attitudes of HIV and STDs testing, safe sexual behaviors and partner notification. The attitudes are collected by questions in the baseline and follow-up questionnaires. (9) Sexual behaviors. They are measured through questionnaires, including questions about the number of different kinds of sexual partners, frequency of anal sex, condom use, and partner notification implementation. (10) Substance use behaviors. This indicator is measured by questionnaires about participants’ usage of methamphetamine, heroin, ecstasy, and some other sex-promoting drugs. (11) Psychological status. Self-rating anxiety scale (SAS) and Self-rating depression scale (SDS) are used to measure participants’ psychological status through questionnaires. (12) Referral rate of HIV and related STDs. This indicator is calculated as the proportion of new HIV and STDs infections who have received treatment. (Additional file 2).

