### Study setting and recruitment

We will conduct our research in Beijing, the capital city of China with high population mobility and demographic heterogeneity and high burden of HIV and related STDs among MSM. We will cooperate with a local community-based organization (CBO) named *Man Wellness Center* to recruit participants and provide HIV and other STDs (syphilis, hepatitis B, and hepatitis C) testing services. *Man Wellness Center* is one of the largest and most popular CBO for MSM to give them HIV and STDs prevention and medical services.

Participants will be recruited in two ways: offline and online. The offline recruitment will be implemented in offline venues, such as the clinic sites of the CBO for routine work, and the gay bars, bathrooms, parks for outreach services. The online recruitment will be implemented through online platforms, such as WeChat, QQ, Weibo and Blued. The process of recruitment includes four steps: (1) Determine whether the participant recruited meets the eligibility criteria. (2) Introduce the research and tools for interventions (the app and the WeChat official account) if eligible. (3) Help the participant sign the electronic informed consent through the app and then show him the functions of the app and WeChat official account. The content of the electronic informed consent contains all necessary information as traditional paper version of informed consent, and the signed electronic informed consent will be stored in the database. Participants under the age of 18 are asked to register the app system and sign the consent accompanied by a guardian, and written consent is also obtained from the guardian. (4) Invite the participant to fill in the baseline questionnaire through the app. (5) Provide HIV and other STDs testing services and upload the test results through the backend database. The recruitment will start from the beginning of the research, and we will stop recruitment in the last 6 months of the research. If the participant has HIV and other STDs testing during the follow-up period, he will be invited to finish a follow-up questionnaire.

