### Analysis

Descriptive analysis will be used to summarize the socio-demographic characteristics, HIV and STDs incidences, as well as knowledge, attitudes and related behaviors of total participants and different subgroups. To investigate the effects of the additional partner notification intervention, we will compare the differences of these primary and secondary outcomes in the control period and in the intervention period. As the HIV and STDs infection and most of the secondary outcomes are categorical variables, the generalized linear mixed models (GLMM) will be used for analysis. The model will include intervention status (in intervention period or not) and time as fixed effects and clusters (the districts) and individuals as random effects. The estimated effects of partner notification will be reported as risk ratio (RR) for binary outcomes and mean difference for continuous outcomes. 95% confidential intervals (CI) and *p* values will also be reported. The total and average additional costs of the intervention will be calculated to reflect the cost-effectiveness of the additional interventions, and the differences of these indicators in the control period and intervention period will be compared. Based on the connections recorded in the partner notification records of the database, social network visualization will be conducted to reflect the real connections of the participants. Social network analysis, such as calculation of degree, density, clique, degree centrality, closeness centrality, betweenness centrality, clustering coefficient, and so on, will be used to describe the characteristics of the social networks. Several transmission models of HIV and STDs will be formed to reflect the diseases transmission among MSM.

Sub-analysis will include: comparison of the effects in different age groups, different sex roles (insertive only, receptive only, both), different usage of HIV and STDs testing services (“Mailing rapid test reagent kit” only, the facility-based only, both). A sensitivity analysis will be conducted to evaluate the cluster (the district)-level effect. We will use the outcomes of each district across the follow-ups as the dependent variable, and fit a linear mixed model with the random effect of clusters (the districts).

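### Testing adherence is scored all-or-nothing on gaps between two tests, so it falls with length of follow-up, ignores silence after the last test, and mixes control and intervention time for men who cross over

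*Protocol article*

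**What the plan says.** Under Outcomes, testing adherence is the third secondary outcome, calculated as "the proportion of participants whose every adjacent testing interval is no more than 3 months", with the 3-month limit attributed to China CDC. The text gives no observation window, no minimum number of tests, no rule for the time after a man's last test, and no link to study period or condition.

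Under Analysis, "we will compare the differences of these primary and secondary outcomes in the control period and in the intervention period", and "The model will include intervention status (in intervention period or not) and time as fixed effects and clusters (the districts) and individuals as random effects".

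Three design features bear on this definition:

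- **Length.** "The open cohort SW-CRCT will last 2.5 years", and "Five continuous observational periods at a 6-month interval are divided" (Study design and timeline).
- **Entry.** "The recruitment will start from the beginning of the research, and we will stop recruitment in the last 6 months of the research" (Study setting and recruitment). Men therefore enter at any time from month 0 to month 24.
- **Testing.** There are no fixed test visits. Men receive monthly prompts and test when they choose: "If the participant has HIV and other STDs testing during the follow-up period, he will be invited to finish a follow-up questionnaire".

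The Sample size section allows for 30% loss to follow-up. The Data management section confirms that test dates are held in the database.

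**The concern.** An indicator that requires every interval to be on time gives a man more chances to fail the longer he is observed. An indicator built only from gaps between two tests cannot see the gap that matters most for adherence, the one that begins when a man stops testing. So the figure can worsen because men stay and improve because they leave.

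The planned mixed model has intervention status, time and an individual random effect. It needs a value for each man in each period, and the definition does not supply one. For a man who crosses over, a single value over all his intervals belongs to neither condition. At stake is the interpretation of a secondary outcome that is named in the abstract and in the objectives.

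**Working it through.** The article gives no figure for adherence, so there is none to reproduce. The 30% loss used below is the plan's own: 4320 / (1 − 0.30) = 6171.4, rounded up to 6172, which matches the Sample size section.

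**1. Length of follow-up.** Recruitment ends at month 24 and the trial at month 30, so planned follow-up runs from about 6 to 30 months. At one interval per 3 months that is k = 2 to 10 intervals. Let q be the chance that one interval is on time, independent and constant. The documents give no q, so a range is shown. The chance that all intervals are on time is q^k.

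| Months (k) | q = 0.95 | q = 0.9 | q = 0.8 |
|---|---|---|---|
| 6 (2) | 90% | 81% | 64% |
| 12 (4) | 81% | 66% | 41% |
| 18 (6) | 74% | 53% | 26% |
| 24 (8) | 66% | 43% | 17% |
| 30 (10) | 60% | 35% | 11% |

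Behaviour is the same down each column. The fall occurs for any q below 1.

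**2. Silence after the last test.** A simulation assumed q = 0.8, on-time gaps uniform on 1 to 3 months, late gaps uniform on 3 to 9 months, and constant-rate loss reaching 30% by month 30. Only closed gaps were scored, as the definition has it.

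- Drop-outs classed as adherent: 48%, or 42% if men with only a baseline test are left out. Completers: 6.5%.
- Overall adherence: 19% with loss, 6.6% without.
- If the open gap to month 30 must also be at most 3 months, adherence with loss is 3%.

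The 48% and 19% count a man with no closed interval as adherent by default. The definition itself leaves him unclassified.

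**3. Men with time in both conditions.** Assume entry is uniform over 24 months. Group g (1 to 4) crosses over at month 6g, so a share 6g/24 = g/4 of its men enter before crossover. The average is (0.25 + 0.50 + 0.75 + 1.00) / 4 = 62.5%.

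**4. Effect on the comparison if the value is split by condition.**

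- Mean control time among men who have any: 3 × (1 + 4 + 9 + 16) / (1 + 2 + 3 + 4) = 9.0 months.
- Mean intervention time by group: 17.25, 15, 11.25 and 6 months, on average 12.4.
- With no true effect, average q^(months/3) over stretches of at least 3 months gives:

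| q | Control | Intervention | Ratio |
|---|---|---|---|
| 0.95 | 0.834 | 0.813 | 0.97 |
| 0.9 | 0.695 | 0.660 | 0.95 |
| 0.8 | 0.482 | 0.431 | 0.89 |

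If everyone enrols at month 0, control times by group are 6, 12, 18 and 24 months and intervention times are 24, 18, 12 and 6. The lengths are the same set and the ratio is 1.00. None of these ratios is adjusted for time, and they do not include drop-out.

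**5. Per-period reading.** If the indicator is taken within each 6-month period, a fully observed period holds two intervals in either condition (0.81 at q = 0.9, 0.64 at q = 0.8), so the length problem goes. The open gap remains: two tests in the first month followed by silence still pass, and a single test in the period leaves no interval to score.

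**The case against.** The strongest reply is that the Outcomes section does not say the value is taken over the whole of follow-up. A model with intervention status, time and individual effects implies repeated values, so a per-period use was probably meant. The window, the minimum number of tests and the treatment of intervals that straddle crossover could then be details for an analysis plan or additional file that is not shown. This has force against the length problem, but not against the open gap: the article fixes a rule based on adjacent tests, and step 5 shows that the flaw survives the per-period reading.

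Four stronger readings are tempting and are not supported.

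- *The outcome cannot be assigned to a condition at all.* Test dates are recorded, men seen under one condition can be assigned, and the time of the others can be split by date. The limit lies in the definition, not in the data.
- *Drop-outs as such count as adherent.* Only those on time until they left do. In the simulation that is fewer than half.
- *Follow-up length drives the indicator and behaviour does not.* At 10 intervals, raising q from 0.8 to 0.9 lifts adherence from 11% to 35%, so both matter.
- *The contrast of 64% with 11% is the bias in the treatment effect.* It compares short with long follow-up. The trial compares control with intervention time, where the no-effect ratio is much closer to 1.

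**Conclusion.** The point holds, for a secondary outcome. As written, the indicator falls with length of follow-up, never penalises silence after the last test, leaves men with one test unclassified, and for men who cross over mixes the conditions to be compared.

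The dependence on length follows from the definition alone; its size rests on the assumed q and on independent intervals. The share of men with time in both conditions rests on uniform recruitment. The drop-out figures rest on the simulated gap and loss patterns. The bias in the control-versus-intervention comparison is uncertain: about 0.97 to 0.89 with no effect under the assumptions of step 4, nil if all enrol at the start, and changed further by time adjustment and by any difference in loss between conditions. HIV incidence is defined on person-years, so this definition affects neither the primary outcome nor the sample size.

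**What to change.** Define adherence for each participant and 6-month period as the proportion of his observed time covered by a test in the preceding 3 months. Districts cross over at period boundaries, so each man-period then belongs to one condition. Count the open gap from the last test to the end of the period, seroconversion or the end of the study. Include men with only a baseline test. Analyse the result as a repeated measure in the planned mixed model.

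A yes/no version (no gap over 3 months within the period, open gap included) stays closer to the present wording. It is not the same quantity, and a man who enters mid-period passes more easily, so partly observed periods need a stated rule. In either version the baseline test covers a man's first 3 months by construction, so say whether counting starts after that. Requiring one test in each fixed 3-month window is a less suitable alternative: a test at the start of one window and at the end of the next would pass with a gap of nearly 6 months.

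The cost is one reworded definition, since the dates are already collected and the article states that recruitment had not begun. The downside is that men who test elsewhere or leave without notice count as not tested, so reported adherence will be lower. A sensitivity analysis that censors at last contact would show the range.
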